#### Tertiary

Establishment of a new cohort of children born of mothers in the trial for future follow-up in order to investigate the effect a higher prenatal vitamin D supplementation has on the off-spring.

### Participant timeline

Figure 2 shows the participant timeline.

**Fig. 2 Fig2:**
[figure not shown]
SPIRIT timeline table for the GRAVITD trial

### Randomisation and blinding

Randomisation is done in a 1:1 ratio, using Research Randomizer (version 4.0). To avoid skewering of data randomisation is done for 200 numbers a time. To assure an even distribution in the two intervention groups trough out the year to secure even distribution of season and hence sunshine exposure, the project supplements are packed in batches of 100 containers with 50 containers with placebo and 50 containers with vitamin D supplements. This is being repeated 10 times in total (n = 2,000). The containers with vitamin D supplement and those with placebo are identical and they are all marked with a unique number referring back to the randomisation. When a woman is included in the trial she will get a random container with tablets. The intervention is blinded for the participants and for all health professionals treating the women during their pregnancy and delivery. Only certain members of the research group, with no role in treatment and diagnosing the women, have access to the master list of randomisation numbers. Unblinding is permissible if a participant develops signs of Vitamin D intoxication and hypercalcemia.

### Data collection methods

#### Blood samples

Venous blood samples will be collected at inclusion. For half of the participants a venous blood sample will be collected in their 3rd trimester as well. Blood samples will be analysed for 25(OH)D at Department of Clinical Biochemistry, Aarhus University Hospital, Denmark using HPLC–MS/MS, which is considered as the gold standard method for measurement of 25(OH)D [41]. Blood samples will also be analysed for calcium, phosphate, iron, zinc and HbA1c at Department of Clinical Biochemistry, Randers Regional Hospital, Denmark.

#### Questionnaires

At inclusion all participants will fill out a questionnaire together with a member from the study group. The questionnaire contains questions about demographic, different aspects of lifestyle (diet, use of dietary supplements, smoking, caffeine intake and alcohol consumption), use of medication, acute- (including covid-19), chronic and genetic diseases, earlier pregnancies, fertility treatment and some pregnancy discomforts (morning sickness, constipation). The questionnaire has a section devoted to sunshine exposure where participants are asked about travel outside of Denmark, sun tanning, use of sunscreen and use of artificial sun.

The participants who return for a blood sample in their 3rd trimester will fill out a new questionnaire containing the same questions about lifestyle, use of medication, diseases and sunshine exposure and some more questions about their current pregnancy.

The questionnaires used in the trial can be obtained by contacting the corresponding author.

#### Biological samples from delivery

At delivery, the midwife will take blood samples from the umbilical cord and store the placenta at 5 °C. A member of the study group will afterwards perform systematic sampling of the placental tissue. After informed consent from participants, placenta samples are either placed in RNAlater or snap frozen and stored at -80 °C for future biological studies on genes and proteins related to vitamin D metabolism. Next Generation RNA Sequencing will be performed on a subgroup of placenta samples.

#### Information from medical records

The following data will be collected from medical records:- Regarding pregnancy: duration of pregnancy, blood pressure (in 1st, 2nd and 3rd trimester, at delivery and after delivery), traces of glucose and protein in urine samples, the placement of the placenta, fetal growth and pregnancy related diseases.- Regarding delivery: mode of delivery, need of initiation of labour, need of oxytocin stimulation, use of analgesia, pyrexia during labour (defined as ≥ 38.2 °C with epidural, without epidural: ≥ 38 °C), use of antibiotics during labour, estimated volume of blood loss at delivery and 2 h postpartum, placental weight and need for caesarean section or assisted delivery.- Regarding the new-born: birthweight, sex, APGAR score at 1-, 5- and 10 min, admission to the neonatal ward, neonatal infection and malformations.

#### Data management

All data will be registered in an electronic case report form designed for the trial using the Research Electronic Data Capture (REDCap) database. The data collection form can be obtained by contacting the corresponding author.

### Statistics

#### Power calculation

There is no current information on what effect an increased vitamin D intake will have on the prevalence of preeclampsia or any of the other pregnancy complications of interest. Hence we have based our power calculation on a hypothesis of a 50–55% reduction in the prevalence of PE which we except to be the least common of the main targets, PE, FGR and GDM.

We expect a prevalence of PE of > 4% among the pregnant women getting the 10 µg vitamin D based on a prevalence of 4.1% in our previous study [17] with inclusion mainly during the summer months, hence the prevalence of PE will probably be a little higher when inclusion is done during both winter and summer months.

With a presumed prevalence of PE at > 4%, a significance level of 0.05 and a power of 80% then 1,000 women in each group will be sufficient to show a statistically significant difference between the two interventions despite a dropout of 5%. The entire study sample will be 2,000 women.

To test the hypothesis, that all participants in the intervention group reach a sufficient 25(OH)D level (≥ 75 nmol/L), a power calculation show that 15 women are needed in each group. The calculation is done with a power of 80% and a significance level of 0.05 and a presumed prevalence of 42% vitamin D insufficiency (25(OH)D < 75 nmol/L) before the intervention, based on data from our previous study [17]. Hence, we have chosen to take a second blood sample in the 3rd trimester in half of the cohort, resulting in 500 in each group.

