Since only 60–80% of maternal 25(OH)D is transferred to the foetus [15], the maternal serum 25(OH)D level needs to be ≥ 75 nmol/L to ensure that the foetus reaches a 25(OH)D level of at least 50 nmol/L. In earlier studies from Denmark, around 30% of pregnant women had aa 25(OH)D level < 50 nmol/L and as many as 70–88% of the pregnant women did not reach a serum 25(OH)D level > 75–80 nmol/L [5, 16] putting the foetus at risk of developing vitamin D deficiency. In a previous cohort study we characterized our present study population, i.e. women giving birth at Randers Regional Hospital, a hospital covering both urban areas, smaller cities and rural areas. Here we found that 10% of the participants had vitamin D deficiency (25(OH)D level < 50 nmol/L) and only 58% reached a sufficient 25(OH)D level of ≥ 75 nmol/L [17]. Notably, this was a study undertaken in the summer months and with a high adherence (86%) to the official Danish recommendations of a daily vitamin D supplement of 10 µg during the entire pregnancy. However, the officially recommended intake of 10 µg vitamin D daily is mainly based on a more than 35 year old small-scale study from Norway [18, 19] and does not take into account the nutritional differences between Denmark and Norway – e.g. a higher prevalence of fish consumption in Norway [20].

PE, one of the pregnancy complications most strongly associated with vitamin D status [7], affects 3–5% of all pregnancies worldwide and PE is still a major cause for maternal and perinatal morbidity and mortality [21, 22]. Danish registers find that 3% of all pregnancies are complicated by PE [23]. We found a similar but slightly higher prevalence in our previous study conducted in 2016–2017 as 4.1% developed PE [17].

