## Discussion

The current recommendation regarding vitamin D in pregnancy in Denmark is based on a few small and older observational studies from other Northern countries with a diet that differs from the typical Danish diet when it comes to vitamin D containing food items such as fatty fish and the use of fish oil supplements. Since this recommendation was made a lot of new evidence have indicated that vitamin D has several additional beneficial effects in pregnancy than just bone development. New recommendations are therefore needed to fit the pregnant population today with an emphasize on the dietary habits, ethnicity and health status of today's population.

With this randomised trial it will be possible to determine if a higher intake of vitamin D in pregnancy can improve the health for pregnant women and their children, by preventing maternal and neonatal complications also associated with health risks in later life. The trial is designed with a statistical power to determine the effect of a higher vitamin D supplement on the risk of developing the major obstetric diseases related to placental dysfunction – PE, FGR and GDM. Such diseases can possibly be prevented for some women by taking an extra vitamin D supplement in pregnancy – a period where most women are already vigilant when it comes to their diet and use of supplements. Further, the trial is large enough to establish if all pregnant women need to take more vitamin D to avoid deficiency or if only some groups of pregnant women need higher doses of vitamin D in their pregnancy e.g. women suffering from overweight or obesity.

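### The 80% power for preeclampsia is attached to a 50–55% reduction, but with 950 evaluable women per arm it is reached only from about 54% at the 4% planning rate

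*Protocol article*

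**What the plan says.** In the Power calculation section the authors write that "we have based our power calculation on a hypothesis of a 50–55% reduction in the prevalence of PE", the complication they expect to be the rarest of the three. For the control group: "We expect a prevalence of PE of > 4% among the pregnant women getting the 10 µg vitamin D", which is "based on a prevalence of 4.1% in our previous study [17] with inclusion mainly during the summer months"; they add that "the prevalence of PE will probably be a little higher when inclusion is done during both winter and summer months". With "a significance level of 0.05 and a power of 80" per cent, they conclude that "1,000 women in each group will be sufficient to show a statistically significant difference between the two interventions despite a dropout of 5" per cent. The total is 2,000 women, allocated 1:1.

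The Statistical analysis section compares PE, fetal growth restriction (FGR) and gestational diabetes (GDM) between groups with a chi-square test at 0.05 and reports risks with 95% confidence intervals. The Discussion says: "The trial is designed with a statistical power to determine the effect of a higher vitamin D supplement" on all three conditions. The Background also mentions that "Danish registers find that 3% of all pregnancies are complicated by PE".

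**The concern.** One power figure is given for a range of effects. Power falls as the effect gets smaller, so the claim is true of the whole range only if it is true at 50%. The sentence on sufficiency is not limited to the 55% end.

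PE is the outcome that fixed the sample size, and the protocol says there is no current information on how large the effect will be. The lower end of the assumed range therefore deserves as much weight as the upper end. If power there is clearly below 80%, readers of a non-significant PE result will credit the trial with more ability to detect a halving of risk than it has.

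**Working it through.** **Inputs.** From Power calculation: control rate above 4% (4.0% is the floor, 4.1% the source value); reduction 50–55%; alpha 0.05; power 80%; 1,000 per arm; 5% dropout, so m = 1,000 × 0.95 = 950 evaluable per arm. Assumption: a two-sided test. The section does not state sidedness, but a chi-square test reported with 95% confidence intervals is two-sided. The whole 0.05 is spent on PE, as in the plan.

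**Formulas** (pooled variance under the null, p̄ = (p1 + p2)/2):

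- Power = Φ{ [√m (p1 − p2) − 1.96 √(2p̄(1 − p̄))] / √(p1(1 − p1) + p2(1 − p2)) }
- n per arm = [1.96 √(2p̄(1 − p̄)) + 0.8416 √(p1(1 − p1) + p2(1 − p2))]² / (p1 − p2)²

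**Step 1: reproduce the plan's figure at 55%.** p1 = 0.040, p2 = 0.018, p̄ = 0.029.

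- n = (0.4651 + 0.1993)² / 0.022² = 912.1, so 913 evaluable; 913/0.95 gives 962 randomised per arm. Rounding up to 1,000 is ordinary.
- Power at 950 = Φ[(0.6781 − 0.4651)/0.2368] = Φ(0.899) = 81.6%.

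**Step 2: the same calculation at 50%.** p1 = 0.040, p2 = 0.020, p̄ = 0.030.

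- Power at 950 = Φ[(0.6164 − 0.4728)/0.2408] = Φ(0.596) = 72.45%.
- n = (0.4728 + 0.2027)² / 0.020² = 1,140.8, so 1,141 evaluable; 1,141/0.95 gives 1,202 randomised per arm, or 2,404 in total against 2,000.

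**Step 3: across the range, 950 per arm.**

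| Control rate | 50% | 52.5% | 55% | Smallest reduction with 80% power |
|---|---|---|---|---|
| 4.0% | 72.5% | 77.2% | 81.6% | about 54% |
| 4.1% | 73.5% | 78.3% | 82.5% | about 53.5% |

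At these two rates, 80% is missed over roughly (54 − 50)/5 = 80% and (53.5 − 50)/5 = 70% of the stated effect range.

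**Step 4: does another method rescue the 50% end at 4.0%?**

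- Exact enumeration of the uncorrected chi-square test: 73.5%.
- Arcsine approximation: 73.6%.
- Continuity-corrected test: 68.6%.
- No dropout at all (1,000 per arm): 74.6%.
- Unpooled variance: 1,139 evaluable needed, or 1,198 per arm after division by 0.95 (1,138.1/0.95, before rounding).
- One-sided test at 0.05: 81.9%. This is the only variant that reaches 80%.

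**Step 5: what control rate would rescue it?** For a 50% reduction with 950 per arm, power is about 78% at 4.5%, 80% at about 4.8% and 82% at 5.0%.

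**The case against.** The strongest reply is that the control rate is also a range. The protocol says more than 4% and expects a rate a little above 4.1%, so one could pair the two ranges: about a 54% reduction at 4.0%, 51% at about 4.5%, and 50% at about 4.8%. The Background's worldwide figure of 3–5% reaches that far. What stands is that 72.5% belongs to one corner, the lowest rate with the smallest effect. But the protocol never states such a pairing and gives no rate near 4.8%, which is a stretch for a little above 4.1%; an open inequality cannot support a specific power figure. A one-sided calculation would also work, but none is stated, and it would not match the planned analysis.

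Three stronger readings are tempting and are not supported.

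- *The sample size is miscalculated.* It is not: 1,000 per arm follows from a 55% reduction with normal rounding.
- *The 3% register rate contradicts the planning rate.* It does not. The 3% is national; the 4.1% comes from the authors' own earlier cohort at this hospital, and they say why they used it. At 3%, power would be about 60% (50% reduction) and 69% (55%), but that is a sensitivity scenario.
- *The Discussion's power claim fails for all three outcomes.* It does not. The Background gives 7–10% for GDM worldwide and about 10% for birthweight below the 10th percentile. Taking 7% and 10% as rough rates for GDM and FGR (an assumption), a 50% reduction has about 93% and 98.6% power, and the reductions detectable with 80% power are about 42% and 35%.

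The planned confidence intervals already give some protection against reading a null PE result as no effect.

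**Conclusion.** The point holds, for PE only. The stated 80% is correct near the upper end of the plan's effect range and not over most of it. At the 50% end the shortfall is about 7.5 points at a 4.0% control rate and 6.5 points at 4.1%: a true halving of PE would be missed in about 27% of such trials, not 20%. This rests on 950 evaluable women per arm, a two-sided 0.05 test and a control rate of 4.0–4.1%. The shortfall narrows to about 2 points at 4.5% and disappears at about 4.8%. The trial's size, test and reported estimates are unaffected; what needs correcting is the description of what the trial can detect.

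**What to change.** Keep 2,000 women. Replace the sufficiency statement in Power calculation with one tied to stated inputs, for example: *With 950 evaluable women per arm and a PE rate of 4% in the control group, power (two-sided 0.05) is 82% for a 55% reduction and 72% for a 50% reduction; the smallest reduction in PE detectable with 80% power is about 54%.*

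In the Discussion, qualify the power statement for PE alone (reductions of about 54% or more at a 4% control rate). Do not extend that limit to FGR and GDM. A 3% control rate may be added as an optional sensitivity figure, where the detectable reduction is about 61%.

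The cost is wording only: no extra participants and no change to the analysis. The stated power becomes less favourable.

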#### Statistical analysis

Data will be analysed according to intention to treat, but if there is a non-compliance and dropout of more than 10%, we will also perform the statistical analysis without those with non-compliance. Demographic data will be presented as counts and percentages for categorical variables and continuous variables will be presented as mean and standard deviation. Data will be tested for normality using QQ-plots and will be log transformed if applicable. For all statistical analysis a level of statistical significance will be defined as 0.05. The primary outcomes PE, FGR and GDM, will be assessed by comparing the event rates in the two groups using a chi-square test and results will be presented as absolute and relative risks along with 95% confidence intervals (Cl). A similar approach will be used for categorical secondary outcomes. A multiple linear regression model will be used to adjust for indifferences in baseline characteristics. The 25(OH)D level will be assessed by comparing the mean in the two groups using students t-test. The same approach will be used for continuous secondary outcomes. Linear regression models will be used to assess continuous variables such as serum levels, blood pressure and biological changes in the placentas.

Subgroup analysis will be performed for the following subgroups:25(OH)D level at enrolment (< 50, 50–75, > 75)Parity (nulliparous vs primiparous and multiparous)EthnicityBMI (Body Mass Index) (≥ 20- < 25, ≥ 25- < 30, > 30, > 35, > 40)Extreme weight gain during pregnancySmoking statusRelevant medicationSocio economic status (income and education)

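### The 25(OH)D hypothesis is that all women on the higher dose reach 75 nmol/L, but both the 15 per group and the planned t-test address a difference between arms, which cannot show that

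*Protocol article*

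**What the plan says.** Maternal 25(OH)D above 75 nmol/L is one of the four primary outcomes in the Outcome section. The Power calculation section states the hypothesis for it as "To test the hypothesis, that all participants in the intervention group reach a sufficient 25(OH)D level", the level being 75 nmol/L or more. It continues that "a power calculation show that 15 women are needed in each group" and gives the inputs: "The calculation is done with a power of 80% and a significance level of 0.05", together with "a presumed prevalence of 42% vitamin D insufficiency (25(OH)D < 75 nmol/L) before the intervention". The 42% is the complement of the Background's finding in the previous cohort at the same hospital, where "only 58% reached a sufficient 25(OH)D level of ≥ 75 nmol/L".

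The section then says "we have chosen to take a second blood sample in the 3rd trimester in half of the cohort, resulting in 500 in each group".

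The Statistical analysis section names one group comparison for this outcome: "The 25(OH)D level will be assessed by comparing the mean in the two groups", by Student's t-test. It also mentions linear regression for continuous variables such as serum levels. It names no analysis of the intervention arm on its own.

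**The concern.** The hypothesis, the sample size and the analysis are all printed, and they do not fit together. The hypothesis is universal and concerns one arm: insufficiency on the higher dose is 0%. A two-group test has a different null, namely that the arms are alike. Rejecting it shows that they differ and leaves open how many treated women are still below 75 nmol/L.

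This is separate from the point that a threshold outcome is to be analysed as a mean. Replacing the t-test with a comparison of proportions at 75 nmol/L would cure that mismatch and leave this one.

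At stake is what the trial may say about the dose. The Background treats a maternal level of 75 nmol/L as what is needed for the foetus to reach 50 nmol/L, and the Discussion expects the results to inform a new recommendation. A dose that suffices for practically everyone and a dose that helps but leaves one woman in five short would support different statements. A between-arm p-value does not tell them apart.

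**Working it through.** **Inputs.** From Power calculation: 42% insufficient, 80% power, alpha 0.05, 15 per group, 500 per group with a second sample. Sidedness is not stated, so two-sided is assumed. The 5% dropout is stated for the pre-eclampsia calculation only; applied here it gives 500 × 0.95 = 475 per group.

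**1. Reproducing the 15.** The usual two-group formula with pooled variance under the null is

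n = [1.96·√(2p̄(1−p̄)) + 0.842·√(p₁(1−p₁) + p₂(1−p₂))]² / (p₁−p₂)²

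- 42% versus 0%: p̄ = 0.21, so n = (1.129 + 0.415)² / 0.1764 = 13.5, i.e. 14.
- 42% versus 1%: n = 14.5, i.e. 15.

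Fisher's exact test gives 15 directly. With nobody insufficient on treatment, 5 of 15 against 0 of 15 has two-sided p = 2·C(15,5)/C(30,5) = 0.042, and 4 of 15 against 0 of 15 has p = 0.100. The test therefore rejects when at least 5 controls are insufficient. P(X ≥ 5) is 0.826 for X ~ Bin(15, 0.42). With 14 per group the cut-off is also 5 (p = 0.041) and the power is 0.770. So 15 is the smallest group size that reaches 80%.

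The figure is thus the size for detecting a between-arm difference. That all treated women reach 75 nmol/L enters only as the assumed alternative.

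**2. What a between-arm test of proportions would do if the hypothesis were false.** Power = Φ{(|p₁−p₂| − 1.96·s₀)/s₁}, where s₀ = √(2p̄(1−p̄)/n) and s₁ = √([p₁(1−p₁) + p₂(1−p₂)]/n). Control insufficiency is taken as 42%.

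For 20% insufficient on treatment and n = 500: s₀ = 0.02925 and s₁ = 0.02841, so (0.22 − 0.0573)/0.02841 = 5.73 and power exceeds 0.999.

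| Treated women still insufficient | 15 per group | 475 per group | 500 per group |
|---|---|---|---|
| 10% | 0.52 | >0.999 | >0.999 |
| 20% | 0.25 | >0.999 | >0.999 |
| 30% | 0.10 | 0.97 | 0.98 |

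At 15 per group the normal approximation is rough. For 20% insufficient, exact enumeration gives 0.13 (Fisher) and 0.27 (uncorrected chi-square).

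**3. Sensitivity to the control rate.** With 20% of treated women insufficient and 500 per group, power is 0.96 if control insufficiency is 30%, and about 1.0 if it is 60% or more.

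**4. What the intervention arm alone could show.**
- With 0 insufficient among n, the exact two-sided 95% upper limit is 1 − 0.025^(1/n): 21.8% for n = 15, 0.8% for n = 475, 0.7% for n = 500.
- With 100 insufficient among 500 (20%), the exact 95% interval is 16.6% to 23.8%. This contradicts a claim about all women, although the between-arm test would be overwhelmingly significant.

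**The case against.** The best defence is that the sentence is loose wording. Read generously, the 0% is only the assumed effect in an ordinary superiority calculation, and step 1 shows that it was used that way. The Abstract's objective is whether the higher dose lowers the prevalence of deficiency, which a two-arm comparison does address, and neither the Abstract nor the Outcome section puts the word 'all' into the outcome. This reading is plausible, and it points to the simplest repair. It does not remove the defect: the sentence is the only hypothesis given for this primary outcome, and no section supplies an analysis that would test it.

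Three other objections stand in part.

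- The rejection rates in step 2 are for a test of proportions, which the plan does not name for 25(OH)D. They show that the natural alternative would not help either. The power of the planned t-test cannot be computed, because no standard deviation is given.
- The 15 drives no design quantity. About 33 times as many women per group (500/15) are to give a second sample, and the total of 2,000 comes from pre-eclampsia.
- A target proportion for the intervention arm could sit in a full protocol or analysis plan that is not shown. Its absence here is not the point; the mismatch in the printed text is.

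A reader might infer more than the document supports: that the investigators will take p < 0.05 between arms as proof that all treated women are sufficient, or that one woman below 75 nmol/L would refute the hypothesis. The protocol article states neither rule.

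**Conclusion.** The concern holds as a mismatch between the stated hypothesis and both the sample size and the planned analysis. The hypothesis concerns the proportion in one arm; the 15 per group and the t-test concern a difference between arms. At 475 to 500 per arm, even a comparison of proportions would be significant with power above 0.999 if 20% of treated women remained insufficient, and with about 0.97 to 0.98 if 30% did. Significance is therefore no evidence that all, or nearly all, are sufficient.

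These figures assume two-sided alpha 0.05, control insufficiency equal to the 42% given as the rate before the intervention and, for 475, the dropout borrowed from the pre-eclampsia calculation. The conclusion does not depend closely on the control rate.

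It would be wrong to attach the near-certain rejection to 15 women per group, where power at 20% insufficient is about 13% to 27%. It would also be wrong to conclude that the trial lacks the data: some 500 intervention-arm samples estimate the proportion closely. The consequence is limited to what may be claimed from this outcome.

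**What to change.** In Power calculation, restate the hypothesis as a between-arm difference in the proportion of women reaching 75 nmol/L or more, and describe 15 per group as the size for detecting 42% versus about 0% insufficient.

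In Statistical analysis, compare that proportion between the arms and report the intervention-arm proportion in the 3rd trimester with an exact 95% confidence interval. Base any statement that the dose is sufficient for all or nearly all women on that interval. If the sponsor wants to make such a claim, it should set the target proportion in advance; nothing in the document fixes one, and none is proposed here. The comparison of means can stay as a supporting analysis.

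The cost is wording. No extra women or samples are needed, since the second samples are already planned. The price is that the claim softens from 'all' to an estimated proportion with its uncertainty.

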## Abstract

**Background:**

The prevalence of vitamin D deficiency is high among pregnant women. Vitamin D deficiency in pregnancy is associated with increased risk of adverse pregnancy outcomes especially complications related to placental dysfunction and insulin resistance. The objective of this study is to investigate if a higher dose of vitamin D supplementation in pregnancy reduces the prevalence of vitamin D deficiency and prevents adverse pregnancy outcome with special emphasize on preeclampsia, foetal growth restriction and gestational diabetes.

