**Methods:**

GRAVITD is a double-blinded randomised trial with parallel groups where all pregnant women attending the free of charge national nuchal translucency scan programme in gestational week 10–14 at Randers Regional Hospital are invited to participate. Enrolment started in June 2020. Participants are randomised in a two armed randomization with a 1:1 allocation ratio into 1) control group – receives 10 µg of vitamin D or 2) intervention group – receives 90 µg of vitamin D. A total of 2000 pregnant women will be included. Maternal blood samples and questionnaires describing life-style habits are collected upon enrolment. For half of the participants blood samples and questionnaires will be repeated again in 3rd trimester. Blood samples will be analysed for 25-hydroxy-vitamin D using high-performance liquid chromatography coupled with tandem mass spectrometry. Upon delivery, placental tissue and umbilicalcord blood will be collected and information on maternal and fetal outcomes will be exstracted from medical records.

The primary outcomes are serum levels of 25-hydroxy-vitamin D ≥ 75 nmol/L and the rate of preeclampsia, foetal growth restriction and gestational diabetes. Secondary outcome includes identification and impact on placental functions related to vitamin D. A tertiary outcome is to initiate a cohort of children born from mothers in the trial for future follow-up of the effects of vitamin D on childhood health.

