### Outcome

#### Primary

The incidence of PEThe incidence of FGR (defined as a negative deviation of more than 15% (10th percentile) from the expected foetal weight diagnosed at ultrasonography scans)The incidence of GDM (defined as 2-h plasma glucose ≥ 9 mmol/l following a 75 g oral glucose load)Maternal serum-25(OH)D > 75 nmol/L

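### The primary vitamin D outcome is a 75 nmol/L threshold, but the only between-group test named for it compares mean levels

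*Protocol article*

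**What the plan says.** All references are to the protocol article.

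- **Outcome.** The Primary outcome list gives "Maternal serum-25(OH)D > 75 nmol/L". The Abstract (Methods) says "The primary outcomes are serum levels of 25-hydroxy-vitamin D ≥ 75 nmol/L". Both describe a yes/no outcome, with different inequality signs.
- **Hypothesis and sample size.** The Power calculation section sets out "To test the hypothesis, that all participants in the intervention group reach a sufficient 25(OH)D level", with the cut at ≥ 75 nmol/L, and assumes "a presumed prevalence of 42% vitamin D insufficiency (25(OH)D < 75 nmol/L) before the intervention". It arrives at 15 women per group (80% power, significance level 0.05) and plans a third-trimester blood sample in 500 per group.
- **Analysis.** The Statistical analysis section applies the chi-square comparison of event rates to pre-eclampsia (PE), foetal growth restriction (FGR) and gestational diabetes (GDM), and extends it to categorical secondary outcomes. For vitamin D it says "The 25(OH)D level will be assessed by comparing the mean in the two groups using students t-test". It adds linear regression for serum levels as continuous variables. The value 75 appears there only as a boundary for subgroups by 25(OH)D at enrolment.
- **Objective.** The Abstract (Background) asks whether the higher dose "reduces the prevalence of vitamin D deficiency". The Background section defines deficiency as 25(OH)D below 50 nmol/L.

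**The concern.** The outcome, the hypothesis and the sample size all concern the share of women who reach 75 nmol/L. The named test concerns the difference in average level. Women given 90 µg daily can hardly fail to differ in mean from women given 10 µg, so a significant t-test is close to a foregone conclusion and says little about how many women remain insufficient.

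The Background justifies the cut-off on the ground that the mother needs at least 75 nmol/L for the foetus to reach 50, and the Discussion expects the results to inform national recommendations. A significant mean difference could be read as showing that the higher dose makes women sufficient when the analysis had not examined this.

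Two smaller inconsistencies belong to the same point. The threshold is written both as ≥ 75 and as > 75, and the objective of reducing deficiency (< 50 nmol/L) has no outcome that uses that cut.

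**Working it through.** **1. Which kind of calculation gives 15 per group?**

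Inputs from the Power calculation section: 42% insufficient against 0% (all intervention women sufficient), significance level 0.05, power 80%. Two-sided testing is assumed, because sidedness is not stated.

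Pooled two-proportion formula, with mean proportion 0.21:

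n = [1.96·√(2 × 0.21 × 0.79) + 0.842·√(0.42 × 0.58 + 0)]² / 0.42² = (1.129 + 0.415)² / 0.1764 ≈ 13.5, so 14 per group.

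Fisher's exact test, two-sided: with 15 per group and no insufficient women in the intervention group, 5 insufficient controls give p = 2·C(15,5)/C(30,5) = 2 × 3003/142506 = 0.042. Four give p = 2 × 1365/27405 = 0.100. The power is therefore P(X ≥ 5) for X ~ Binomial(15, 0.42) = 0.826. At 14 per group it is 0.770, so 15 is the first size above 80%.

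The stated figure is thus a comparison of proportions. No SD or mean difference is given from which a t-test sample size could be derived.

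**2. What can a significant t-test leave unanswered?**

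Assumptions (the article gives no SD): normal levels with SD 20, 25 or 30 nmol/L, and 42% of controls below 75. The control mean is then 75 + 0.202 × SD = 79.0, 80.0 or 81.1. After a mean shift d, the share of the intervention group below 75 is Φ(−0.202 − d/SD).

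| Mean shift (nmol/L) | Still below 75: SD 20 | SD 25 | SD 30 | t-test power, 500 per group |
|---|---|---|---|---|
| 10 | 24.1% | 27.4% | 29.6% | about 1.00 |
| 20 | 11.5% | 15.8% | 19.3% | about 1.00 |
| 40 | 1.4% | 3.6% | 6.2% | about 1.00 |

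The smallest difference the t-test detects with 80% power is 2.80 × SD × √(2/n). If 5% of the 500 samples are lost (an assumption that borrows the dropout rate from the PE calculation), n = 475 and the result is 3.6, 4.5 or 5.5 nmol/L for SD 20, 25 or 30.

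A second illustration: with an intervention mean of 110 and SD 30 (both assumed), Φ((75 − 110)/30) = Φ(−1.17) = 12.2% of women remain below 75.

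**3. Can the data address the hypothesis that all women reach 75?**

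If every one of n women reaches the threshold, the exact two-sided 95% lower limit is 0.025^(1/n). This is 78.2% for 15 of 15 and 99.2% for 475 of 475. The literal hypothesis is also fragile: if each woman had a 99% chance of reaching 75, the chance that all 500 do is 0.99^500 = 0.7%.

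**4. Is the sample enough for the matching analysis?**

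Power of the two-proportion test with 500 per group and 42% insufficient among controls:

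| Insufficient in the intervention group | Power |
|---|---|
| 0%, 10% or 20% | about 1.00 |
| 30% | 0.978 |
| 33% | 0.837 |
| 33.5% | 0.793 |

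**The case against.** The strongest reply is that this is a condensed article. The text does not say that the t-test replaces a threshold comparison, and the prevalence-based sample size suggests that a comparison of proportions was in mind. That would carry weight if the analysis section were silent on 25(OH)D. It is not: it names a test, and it names the outcomes that receive the chi-square test without including this one. What stands is that the claim concerns the analysis as published; an unseen analysis plan might add the missing comparison.

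Second, a between-group test of proportions would not show that all women reach 75 either. With 500 per group it has 0.837 power at 42% against 33%, so a third of the intervention group could remain insufficient behind a significant result. This is correct. It means that the hypothesis needs rewording, and that the estimated proportion with its interval, rather than a p-value, must carry the conclusion.

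Third, the stated aim and the main sample size concern pregnancy complications, so the threshold is only part of the trial's rationale. This also stands, but 25(OH)D is still one of four declared primary outcomes.

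Fourth, the choice of inequality will reclassify very few women, and 75 nmol/L may be meant as the working form of the deficiency objective. Both are fair. These two points are secondary, and the main finding does not depend on them.

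**Conclusion.** The concern holds. The threshold outcome is defined, hypothesised and sized as a proportion, but the only between-group test named for 25(OH)D compares means. The stated primary outcome therefore has no matching test in the published plan. If the plan is followed as written, a virtually certain significant result could coexist with roughly 11% to 30% of intervention women below 75 nmol/L, for mean shifts of 20 down to 10 nmol/L. That range rests on assumed normality, an assumed SD of 20 to 30 and 42% of controls below 75; the mismatch itself rests on no assumption.

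The fault is confined to the analysis and interpretation of this one outcome. The 15 per group reproduces, the planned 500 per group is more than adequate, and the PE, FGR and GDM comparisons are unaffected.

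**What to change.** Before unblinding, amend the protocol or analysis plan as follows:

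- Make the primary 25(OH)D analysis the proportion with third-trimester 25(OH)D ≥ 75 nmol/L by randomised group, reported as risk difference and relative risk with 95% CI.
- Replace the hypothesis that all intervention women reach the threshold with a between-group difference in that proportion. Report the intervention-group proportion with an exact 95% CI to show how close to all it comes.
- Use one inequality throughout.
- Report the proportion below 50 nmol/L in the same way, so that the deficiency objective has a matching result.
- Keep the comparison of means as a supportive analysis.

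The cost is wording only, with no new samples or data. The binary comparison is less powerful than the comparison of means, but 500 per group (or about 475 after an assumed 5% loss) is far above the 15 that the plan calculates.
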